## Introduction

### Background and rationale

Gastric cancer is a common malignant tumour with the third highest mortality rate worldwide. In 2018, more than 1.3 million new cases of gastric cancer were diagnosed and more than 780,000 deaths occurred [1]. Although the incidence of gastric cancer has decreased in the past 30 years, it is still very high in East Asia [2]. Indeed, there are more than 400,000 new cases of gastric cancer in China each year. The overall 5-year survival rate of these patients is about 30%, which is significantly lower than that in South Korea and Japan [3]. Overall, improving the comprehensive treatment effect of gastric cancer, ensuring the quality and safety of the perioperative period, improving the prognosis of these patients, and establishing an effective clinical pathway are important topics of research in China, and the primary goals are preventing and treating gastric cancer. At present, many treatment methods, such as surgery, radiotherapy, chemotherapy, targeted therapy, and immunotherapy, are available for patients with gastric cancer. Surgical resection is an effective way to improve the survival rate of these patients. Among the surgical options available, D2 radical gastrectomy has become the standard method for advanced gastric cancer. Since Goh et al. first reported laparoscopic radical gastrectomy for advanced gastric cancer in 2001, laparoscopic gastric cancer surgery has been developed rapidly and is used worldwide, especially in countries with a high incidence of gastric cancer, such as Japan, South Korea and China [4]. One of the unique advantages of laparoscopic surgery is its minimally invasive nature, but in view of the need for D2 lymph node dissection for patients with advanced gastric cancer, this operation is difficult and complex, so initial laparoscopic surgery is used only for the treatment of early-stage gastric cancer. After more than 10 years of research, large samples of multicentre clinical data have confirmed the safety, feasibility and effectiveness of laparoscopic radical gastrectomy for the treatment of early gastric cancer [5]. The latest Chinese Laparoscopic Gastrointestinal Surgery Study-01 (CLASS-01) findings state that “laparoscopic distal gastric cancer D2 radical resection performed by an experienced team is safe and feasible for the treatment of locally advanced gastric cancer” [6]. Upon reviewing the development of and advancements in gastric cancer surgery, we find that it has gradually changed from “standard and open surgical resection” to “individualized and accurate minimally invasive surgery” with further improvements to the safety of the operation and the quality of life of the patients postoperatively [7]. The new approach guided by the concept of laparoscopic minimally invasive surgery not only reduces the size of the surgical incision but also minimizes tissue trauma and maximizes functional preservation on the basis of radical oncology [8].

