**Fig. 1 Fig1:**
[figure not shown]
Flowchart of patient enrolment and randomization. *Abbreviations*: *ERAS* enhanced recovery after surgery, *POD* postoperative day.

For randomization, a central dynamic, stratified strategy is adopted. The randomization sequence is generated by using the Pocock–Simon minimization method in SAS version 9.3 (SAS Institute Inc., Cary, NC, USA) and stratified by participating site (13 hospitals) and surgical procedure (laparoscopic or robotic). Participating centres will submit the above information to the data centre at the Department of Gastrointestinal Surgery, Affiliated Hospital of Qingdao University, Qingdao, China, where central randomization will be performed. Information on treatment allocation is subsequently sent to each participating centre.

The inclusion criteria were as follows: (1) newly treated patients with no chemotherapy, radiotherapy or other anti-tumour treatment performed before the beginning of the clinical trial; (2) patients between 18 and 75 years of age; (3) patients at a clinical stage of advanced T (1–4a), N (0–3) or M0 scheduled to undergo radical resection of distal gastric cancer; (4) male or non-pregnant and lactating females; (5) patients with pathologically diagnosed gastric adenocarcinoma; (6) patients with Eastern Cooperative Oncology Group (ECOG) score 0–1; and (7) patients who voluntarily sign the informed consent form.

The exclusion criteria were as follows: (1) other malignant tumours within 5 years, (2) M1 disease found during the operation, (3) severe or uncontrolled medical diseases and infections found at the same time, (4) use of opioid analgesics or hormones within 7 days before the operation, (5) severe or uncontrollable mental illness, (6) any unstable condition or condition that may endanger the safety and compliance of the patient, and (7) participation and treatment with anti-cancer drugs in other clinical trials.

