### Sample size estimate

This study adopts the design of a non-inferiority test, and the calculation of sample size is based on the following historical data and assumptions. Previous studies have shown that the overall 3-year survival rate for patients with gastric cancer is about 50% [5]. The centre followed patients who underwent radical resection of gastric cancer under the management of ERAS from 2011 to 2014, and the 3-year survival rate was about 65% [21]. Given that patient selection will require 10 months, the median follow-up time should be about 3 years, and therefore the non-inferiority threshold is set to 1.33, according to a 1:1 random ratio. Given a significance level of α = 0.05 (bilateral) and test efficiency of 1 − β = 80%, the withdrawal rate of either branch group should be 10% and thus the total sample requires at least 400 patients (200 in the test group and 200 in the control group).

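### The 50% and 65% survival rates behind the sample size describe different populations, so their gap mixes case mix with treatment effect and the control rate probably overstates deaths

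*Protocol article*

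**What the plan says.** All references are to the protocol article.

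- **Sample size estimate, reference rate:** "Previous studies have shown that the overall 3-year survival rate for patients with gastric cancer is about 50% [5". Nothing restricts this to operated or non-metastatic disease.
- **Sample size estimate, ERAS rate:** "The centre followed patients who underwent radical resection of gastric cancer under the management of ERAS from 2011 to 2014". Survival of this cohort at 3 years is put at roughly 65%, with reference 21 as the source.
- **Sample size estimate, hypothesis:** "This study adopts the design of a non-inferiority test", and "the non-inferiority threshold is set to 1.33". The section adds two-sided alpha 0.05, 80% power, 10% withdrawal and a total of at least 400.
- **Participant selection and randomization, inclusion criterion 3:** "patients at a clinical stage of advanced T (1–4a), N (0–3) or M0 scheduled to undergo radical resection of distal gastric cancer". Patients must also be ECOG 0–1 and aged 18 to 75, and M1 disease found at operation is an exclusion.
- **Background and rationale:** 5-year survival of about 30% is given for Chinese patients overall. Reference 5, the source of the 50%, is cited here for the "feasibility and effectiveness of laparoscopic radical gastrectomy for the treatment of early gastric cancer [5".
- **Statistical analyses:** log-rank test and Cox hazard ratio. The Follow-up section schedules visits to 36 months.

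**The concern.** Two historical rates placed side by side are informative about treatment only if they describe similar patients. Here one is worded for gastric cancer patients at large and the other for patients who had a radical resection. Part of the 15 points may be the difference between those groups, which randomization will remove.

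The trial's own controls will be resectable and M0, with good performance status. An all-patient rate is likely to be too low for them. The log-rank and Cox analyses draw their information from deaths, so higher control survival means fewer deaths from the same 400 patients. At stake is whether the stated 80% power applies to the trial that will be run, and whether an inconclusive result could be interpreted.

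**Working it through.** **Inputs.** From the sample size section: survival 50% and 65%, margin 1.33 (read as a hazard ratio, since the scale is not named), two-sided alpha 0.05 (one-sided 0.025 for non-inferiority), N = 400, 10% withdrawal, hence 400 × 0.90 = 360 evaluable. Assumed: control survival above 50%, proportional hazards, and all 360 followed for 36 months.

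**Step 1. Where 400 comes from.**
- Stated non-inferiority test at true HR 1: deaths = 4(1.96 + 0.84)² / (ln 1.33)² = 386. At 50% mortality, 386 / 0.50 / 0.90 ≈ 858 patients.
- The same test at HR = ln 0.65 / ln 0.50 = 0.62: 54 deaths, about 142 patients.
- Superiority, 50% versus 65%, two-sided 0.05, two proportions with continuity correction: 183 per arm, or 404 to 408 after the withdrawal allowance, depending on how it is applied.
- Superiority log-rank at HR 0.62: 139 deaths, about 364 patients (Schoenfeld), or 145 deaths, about 380 (Freedman).

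Of these calculations, only the continuity-corrected superiority comparison lands within 3% of 400. The 50%-to-65% gap therefore appears to drive the sample size, although the text does not say so.

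**Step 2. Which population the 50% fits.** At constant hazard, 30% at 5 years corresponds to 0.30^(3/5) = 0.486, or 49% at 3 years. This agrees with 50% as an all-patient figure. It is supporting evidence, not proof.

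**Step 3. Power as control survival S changes.**
- Deaths D = 360 × [(1 − S) + (1 − S^HR)] / 2
- Superiority power = Φ(√D/2 × (−ln HR) − 1.96)
- Non-inferiority power = Φ(√D/2 × (ln 1.33 − ln HR) − 1.96)
- ln 1.33 = 0.285; ln 0.62 = −0.476, using the unrounded HR of 0.6215

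| Control 3-year OS | Deaths, HR 1 | Non-inferiority power, HR 1 | Deaths, HR 0.62 | Non-inferiority power, HR 0.62 | Superiority power, HR 0.62 |
|---|---|---|---|---|---|
| 50% | 180 | 48% | 153 | 99.7% | 84% |
| 65% | 126 | 36% | 105 | 97% | 68% |
| 80% | 72 | 23% | 59 | 83% | 45% |

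Worked example for S = 65%, HR 0.62: ERAS survival is 0.65^0.62 = 0.765 and D = 360 × (0.35 + 0.235)/2 = 105. Superiority power is Φ(5.13 × 0.476 − 1.96) = Φ(0.48) = 68%.

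**Step 4. ERAS held at the plan's 65%, controls at 60%.** HR = ln 0.65 / ln 0.60 = 0.843 and D = 360 × (0.40 + 0.35)/2 = 135. Superiority power is Φ(5.81 × 0.170 − 1.96) = 17%. Non-inferiority power is Φ(5.81 × 0.456 − 1.96) = 75%.

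**Step 5. The full 15 points kept on a higher base, 65% versus 80%.** HR = 0.518 and D = 360 × (0.35 + 0.20)/2 = 99. Superiority power is Φ(4.97 × 0.658 − 1.96), about 90%.

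**The case against.** - **The declared design is non-inferiority.** The article never names 15 points or a hazard ratio of 0.62 as its design effect. This stands, so both tests are shown. At a true hazard ratio of 0.62 the non-inferiority test keeps more than 80% power even at 80% control survival.
- **The direction is conditional.** A reader might infer that the stated power is simply overstated. The documents do not support that as a flat claim: Step 5 goes the other way, and at HR 1 power is only 48% with the 50% taken at face value. That shortfall comes from the margin and N, which is a separate problem.
- **The source of the 50% is unseen.** Reference 5 is also cited for laparoscopic gastrectomy, that is, for operated patients, so the figure might not be an all-patient rate. This stands as uncertainty. Citing one reference both for early disease and for 50% survival needs explaining in either case.
- **A review route exists.** A data monitoring committee looks at the data at about 200 enrolled and may adjust the protocol. It is unlikely to see this problem. With uniform accrual over 10 months, 200 patients have a mean follow-up of 2.5 months, giving 200 × 2.5 × (0.693 + 0.431)/2/36 ≈ 8 deaths on the plan's own rates.
- **DFS is also a main endpoint** and yields at least as many events as OS. True, but the sample size text uses survival rates only.

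Two remedies are tempting and unsupported. A target of 139 deaths fits only superiority at 0.62; under the declared test at HR 1 it gives Φ(√139/2 × 0.285 − 1.96), about 39%. Nor does the sample size argument call for removing T1 patients.

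**Conclusion.** The point holds in a limited form. As worded, the two rates describe different populations, the gap between them cannot be read as a treatment effect, and 50% probably overstates deaths in resectable M0 controls.

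The size of the loss is an assumption, because no rate for resected patients under traditional care is given; the 65% is an ERAS rate. Moving control survival from 50% to 65% cuts deaths at HR 1 from 180 to 126, which is 30% fewer. Power then falls from 48% to 36% (non-inferiority, HR 1) or from 84% to 68% (superiority, HR 0.62). The most damaging case is a gap that is largely case mix: 60% versus 65% leaves 17% power for superiority. The loss is small for non-inferiority if ERAS truly achieves 0.62, and it reverses for superiority if a full 15-point gain persists. All figures assume 360 evaluable patients, proportional hazards and OS as the endpoint.

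**What to change.** 1. State whether the primary test is non-inferiority or superiority; the remaining figures depend on it.
2. Replace the 50% with 3-year OS of resected M0 patients under traditional care at the participating centres, and say which population reference 5 describes.
3. Restate the 80% power under the chosen test across a range of control survival, for example 50% to 80%.
4. Derive the event target that matches that test and monitor pooled, blinded deaths against it. If it is not reached at 36 months, either continue survival contacts or report the lower power.
5. Reconcile the wording of inclusion criterion 3, which joins advanced with T1 and links M0 by an or, with the exclusion of M1 disease.

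The cost is a records review at the centres, a stated power that may be less favourable, and possibly longer survival follow-up. If the chosen test turns out to need far more deaths than 400 patients can supply, as non-inferiority at HR 1 would, the restated power should say so.

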## Trial design

This experiment will include patients randomly divided into two groups – an experimental group and a control group – in a 1:1 ratio. The perioperative period of the experimental group will be managed according to the ERAS pathway and that of the control group will be managed according to the traditional management. After the patient was admitted to the hospital, imaging and haematological examinations will be performed; the risk assessments of nutrition risk screening 2002 (NRS2002), vein thromboembolism, American Society of Anesthesiologists will be administered; contraindications will be excluded; and laparoscopic-assisted radical resection of distal gastric cancer (D2, Billroth I, Billroth II, Roux-en-Y) will be performed under anaesthesia.

The trial will assess the clinical safety of the ERAS pathway and its impact on long-term survival. The effect of the ERAS pathway on inflammatory factors – leukocyte count, neutrophil percentage, C-reactive protein (CRP), procalcitonin, tumour necrosis factor-alpha (TNF-α) and interleukin-6 (IL-6) – will also be explored. The sample size is calculated according to survival rate, follow-up time, inferior value, grouping ratio, test efficiency, and loss of follow-up rate. A complete checklist of items according to SPIRIT (Standardized Protocol Items: Recommendations for Intervention Trials) (2013) is provided [18].

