### Statistical analyses

Classification variables will be analysed by the chi-squared test or Fisher’s exact test, and continuous variables will be analysed by the independent *t* test. DFS will be defined as the time from surgery to death or recurrence of gastric cancer, whichever occurs first. The Kaplan–Meier method will be used to generate survival curves, and the log-rank will be applied to compare the differences between survival curves. The hazard ratio and 95% confidence interval will be calculated with the Cox regression model. Variables will be selected for inclusion in the final multivariable model using a stepwise method, and significance levels of 0.25 and 0.15 will be employed as the criteria for inclusion and retention. A *P* value of less than 0.05 will be considered to indicate statistical significance. Data analysis will be performed by using SPSS® software package version 22.0 (SPSS Inc., Chicago, IL, USA).

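### The 400 patients and 80% power do not follow from the stated non-inferiority inputs; with a margin of 1.33 and equal arms, 400 patients give about 42–52% power for overall survival

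*Protocol article*

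**What the plan says.** All references are to the protocol article.

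- **Design.** Sample size estimate: "This study adopts the design of a non-inferiority test".
- **Margin.** Same section: "the non-inferiority threshold is set to 1.33, according to a 1:1 random ratio". No scale is given for 1.33.
- **Survival rates.** Same section: three-year survival of about 50% from earlier studies of gastric cancer, and about 65% in the centre's own 2011–2014 cohort managed under ERAS.
- **Error rates and loss.** Same section: alpha 0.05 two-sided, power 80%, withdrawal 10% in each arm.
- **Result.** Same section: "thus the total sample requires at least 400 patients (200 in the test group and 200 in the control group".
- **Basis of the result.** Trial design: "The sample size is calculated according to survival rate, follow-up time, inferior value, grouping ratio, test efficiency, and loss of follow-up rate". The margin is therefore presented as an input to the number.
- **Analysis scale.** Statistical analyses: log-rank test, and "The hazard ratio and 95% confidence interval will be calculated with the Cox regression model".

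The assumed true effect under the alternative is not stated.

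**The concern.** The section presents 400 patients and 80% power as the output of a calculation and prints nearly all of its inputs, so the output can be checked. A hazard-ratio margin of 1.33 is fairly tight: from 50% three-year survival it allows a fall to 0.5^1.33 = 39.8%. Ruling that out when the arms are equal takes several hundred deaths, and 400 patients with about half dying cannot supply them.

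If non-inferiority is the real test and ERAS has no effect on survival, the trial has roughly an even chance of reaching its conclusion, not four in five. If superiority is the real test, as the Abstract's stated aim suggests, the margin played no part in the size. Leaving it in the text would then allow a non-inferiority claim that the trial was not sized to support.

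**Working it through.** **Inputs.** From Sample size estimate: margin 1.33, alpha 0.05 two-sided, power 80%, 1:1 allocation, withdrawal 10%, three-year survival 50% and 65%. Assumed here: 1.33 is a hazard ratio (HR), because the planned analysis is log-rank and Cox; the share of patients who die is 50%, or 42.5% (the mean of the 50% and 35% death rates). Deaths and patients are rounded up.

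**Formula (Schoenfeld, 1:1).** D = 4(1.960 + 0.842)² / (ln margin − ln HR)², with numerator 31.40. Patients N = D / death share / 0.9.

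**1. Attempt to reproduce 400 as non-inferiority**

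*Equal arms, true HR 1.* (ln 1.33)² = 0.0813, so D = 31.40/0.0813, just over 386, hence 387 deaths.
- 50% deaths: 387/0.5 = 774; 774/0.9 = 860 patients.
- 42.5% deaths: 387/0.425 = 911; 911/0.9 = 1,012 patients.

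*True survival 65% versus 50%.* HR = ln 0.65 / ln 0.50 = 0.6215. ln(1.33/0.6215) = 0.761, so D = 31.40/0.579, hence 55 deaths; 55/0.425 = 130; 130/0.9, about 144 patients.

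The first is more than twice 400, the second about a third of it.

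**2. Other readings of the non-inferiority inputs**
- One-sided alpha 0.05, HR 1: 305 deaths, 678 patients at 50% deaths.
- Comparison of proportions, equal rates of 50% or 65%, with 1.33 read as a hazard ratio, a risk ratio of death or a ratio of survival, at one-sided 0.025 or 0.05: 243 to 1,072 patients, the nearest to 400 being 447.
- The same with 65% versus 50%: 67 to 132 patients.

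None comes within 3% of 400.

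**3. Superiority, 65% versus 50%, margin unused**
- Log-rank: (ln 0.6215)² = 0.226; 31.40/0.226 gives 139 deaths; 139/0.425 = 328; 328/0.9, about 364 patients.
- Two proportions: 170 per arm, 340 in total; 340/0.9 = 378.
- Two proportions with continuity correction: 183 per arm, 366 in total; 366/0.9 = 407.

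The last is the only variant tried that lands within 3% of 400.

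**4. Non-inferiority power of the stated size at true HR 1**

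Power = Φ(½√D × ln 1.33 − 1.960).

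| Patients analysed | Death share | Deaths | Power |
|---|---|---|---|
| 400 | 50% | 200 | 52% |
| 360 (after 10% loss) | 50% | 180 | 48% |
| 400 | 42.5% | 170 | 46% |
| 360 | 42.5% | 153 | 42% |
| 400 | 35% | 140 | 39% |
| 360 | 35% | 126 | 36% |

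For example, D = 200: ½ × 14.14 × 0.285 − 1.960 = 0.057, and Φ(0.057) = 52%.

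*Sensitivity.* With exponential survival, uniform accrual over 10 months and follow-up of everyone to 36 months after the last enrolment, power at 50% survival is 52% (360 analysed) to 56% (400 analysed). At one-sided 0.05, over the six rows above, it is 48–65%. About 387 of the 400 patients would have to die for 80%.

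**5. True HR at which 400 would give 80% non-inferiority power**

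HR = 1.33 / exp(√(31.40/D)): 0.85 at 153 deaths, 0.87 at 170, 0.88 at 180, 0.89 at 200.

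**6. Superiority power of the stated size**

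At HR 0.6215 with 153 deaths: Φ(½ × 12.37 × 0.476 − 1.960) = Φ(0.98) = 84%.

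**The case against.** The strongest reply is that 42–52% describes a scenario the article does not state. It assumes that 1.33 is a hazard ratio, that the arms are equal, and that 42.5–50% of patients die. The only rates printed are 50% and 65%, and if those are the truth, 400 patients give more than 99% power to meet the margin. The number is also about right for a superiority test, particularly as the text says at least 400, so the fault may lie in the design label and the margin rather than in the arithmetic. Finally, the figures concern overall survival only, whereas the main endpoint also names disease-free survival, which will have at least as many events.

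Much of this is fair. The power range is conditional: it falls to 36–39% if both arms have 65% survival and rises to about 56% with longer follow-up at 50%. No rate for disease-free survival is given, so its power cannot be computed. The absence of a required number of deaths is an omission that a condensed article may leave to the full protocol, and it is not part of this point.

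The reply does not rescue the calculation. The 65% versus 50% reading needs 144 patients, so it does not explain 400 either. A modest assumed benefit, HR 0.85–0.89, would explain it, but the article states none and its own rates imply 0.62. If the label is what is wrong, the stated design and the stated power still do not belong together.

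**Conclusion.** The point holds and must be fixed. The printed inputs of the non-inferiority test give about 860–1,012 patients if the arms are equal, or about 144 if the two historical rates are the truth; neither is 400. With equal arms, a hazard-ratio margin of 1.33 and 153–200 deaths, 400 enrolled gives about 42–52% power for overall survival, against the 80% claimed. The exact figure depends on the death share, but none of the equal-arm scenarios examined reaches 80%. The number is close to a superiority calculation on 65% versus 50%, which also matches the aim in the Abstract of showing improved survival.

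**What to change.** Rewrite the Sample size estimate paragraph so that the hypothesis, the scale of any margin, the assumed true effect, the number of deaths and the number of patients agree.

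- **If superiority is intended**, which fits the Abstract: drop the 1.33 margin and state three-year overall survival of 65% versus 50% (HR 0.62), two-sided alpha 0.05, 80% power, 139 deaths, and 364 patients by log-rank (378 by two proportions) after 10% withdrawal. Add that 400 enrolled gives about 153 deaths and 84% power. The reference to an inferiority value in the Trial design section should go as well. Cost: restated text, no change in enrolment.
- **If non-inferiority is intended**: state that 1.33 is a hazard ratio, state the assumed true HR, and give the power that follows, about 42–52% at HR 1 with 400 enrolled. This too is only restated text, but it records an underpowered test. Restoring 80% at HR 1 would need about 860 to 1,012 patients.
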